The potential mechanisms by which vitamin D can affect glucose metabolism could be the result of a rapid non-genomic effect or slower genomic effect of serum 25 (OH) D: 1) stimulation of insulin release by the increased expression of vitamin D receptor (VDR) as well as the enzyme 1α-OHase in the pancreatic beta-cells; 2) by binding of the 1,25 (OH) 2D - VDR complex to the vitamin D response element of the insulin receptor at tissue level enhancing insulin responsiveness for glucose transport; 3) suppression of the release of pro-inflammatory cytokines that are believed to mediate insulin resistance [2,5,23]. The latter hypothesis is supported by studies showing an association between low serum 25 (OH) D and increased C-reactive protein levels [24]. Indirectly, vitamin D may influence the extracellular and intracellular calcium regulation which is essential in mediating glucose transport in target tissues.

Another hypothesis may be the influence of serum vitamin D on oxidative stress and thereby reducing the formation of advanced glycaemic end products (AGEs). AGEs are a heterogeneous group of compounds formed nonenzymatically by glycation and oxidation of proteins. In patients with T2DM AGE formation is enhanced as a consequence of a hyperglycaemic and free radical rich environment [25]. The AGE accumulation in the skin, as measured by skin autofluorescence, has found to be an independent strong predictor of microvascular and macrovascular complications in both type 1 and type 2 diabetes [26-28]. Until now, solely a study conducted in diabetic rats is available which demonstrated a relation between AGEs and vitamin D [29].

We proposed to start a RCT with the following objectives:

i. To investigate the effect of vitamin D supplementation on glycaemic control and insulin resistance in patients with T2DM.

ii. To investigate the effect of vitamin D supplementation on health related quality of life measured by SF-36 in patients with T2DM.

iii. To investigate the association between skin autofluorescence and serum vitamin D

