### Sample size estimation

It was calculated that 126 patients with T2DM would be required in this trial to demonstrate a significant difference at 80% power and 5% significance. Power calculations were based on the literature and aimed at a difference of 0.5% in HbA_1c_ value in the treated group as compared to the placebo group with a standard deviation of 1.0% [30]. With an expected rate of 50% vitamin D deficient participants, 252 subjects would be required. According to an expected drop out rate of 20%, 300 subjects will be recruited.

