### Statistical analysis

The primary efficacy analysis to explore the intervention effect on glycaemic control will be based on the intention-to-treat (ITT) method, in which all randomised patients for whom outcome data are available, will be recorded. In the ITT analysis the patients will be analysed according to their original group assignment, whether or not they accepted and/or adhered to the intervention. This analysis avoids the possibility of any bias associated with loss, misallocation or non-adherence of participants. If there will be a substantial difference between those allocated to receive an intervention and those who actually received it (and adequately adhere to it), we will perform an additional analysis adjusting for actual treatment received (‘per protocol’ analysis). The results of the ‘per protocol’ analysis will be compared with the ITT analysis and the numbers involved will be precisely described.

All raw data will be entered into SPSS software (version 20.0, SPSS Inc, Chicago, IL). Ten percent of all data will be double-entered to check for duplication and outliers before starting statistical analyses.

Baseline characteristics of the study patients will be summarised separately for each randomised group. Dichotomous and categorical data will be presented as number and percentages of patients within both groups. Continuous variables will be checked for normality and will be presented in terms of means and standard deviation if normally distributed, or when a variable has a skewed distribution as median, 25th and 75th percentiles. Nominal variables including subgroups will be analysed using the Chi-squared test, ordinal variables by the Mann-Witney test or Kruskall-Wallis test and continuous variables by the *t*-test or analysis of variance model (ANOVA).

The primary efficacy endpoint, HbA_1c,_ will be compared between placebo and treatment group using a repeated measures analysis of variance with adjustment for baseline characteristics. For secondary outcomes a paired *t*-test, Wilcoxon’s test or repeated measures analysis of variance will be performed. Delta values will be calculated to compare the differences in means over time between the treatment and placebo group.

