Correlation coefficients will be measured using Pearson or Spearman, depending on the level of measurement. A logistic and/or linear regression model will be used for multivariate analysis to relate an outcome variable to causal variables. The multivariate analysis will be used to rule out the possible role of confounders for vitamin D deficiency as season of measurement, maternal age, ethnicity, diet, physical activity and BMI.

Subgroup analyses will be performed by stratifying vitamin D into three groups: deficient (15–49 nmol/l), insufficient (50–74 nmol/l), and sufficient (75–150 nmol/l). Furthermore, subgroup analyses for vitamin D deficient patients (serum 25 (OH) D 15–35 nmol/l), and poor glycaemic control (HbA_1c_ ≥ 53 mmol/mol) will be performed using the same method as described for the primary analysis. A p-value < 0.05 will be considered as statistical significant.

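### For the secondary outcomes, within-arm paired tests stand beside an unspecified between-arm comparison of changes, and nothing says that the between-arm comparison decides

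*Protocol article*

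**What the plan says.** The relevant text is in the Statistical analysis section of the protocol article.

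- **Primary endpoint.** HbA1c "will be compared between placebo and treatment group using a repeated measures analysis of variance with adjustment for baseline characteristics". This is explicitly a contrast between arms.
- **Secondary outcomes, tests.** "For secondary outcomes a paired *t*-test, Wilcoxon’s test or repeated measures analysis of variance will be performed". The sentence does not mention a comparison between arms and gives no rule for choosing among the three methods.
- **Secondary outcomes, changes.** The next sentence reads: "Delta values will be calculated to compare the differences in means over time between the treatment and placebo group". This is a between-arm comparison, but it names no test and mentions no adjustment for the baseline value.
- **Threshold.** "A p-value < 0.05 will be considered as statistical significant". No distinction is made between primary, secondary and descriptive tests.

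The secondary outcomes carry stated objectives. Insulin resistance belongs to objective i. Quality of life is objective ii: "To investigate the effect of vitamin D supplementation on health related quality of life measured by SF-36 in patients with T2DM".

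**The concern.** Patients are randomised 1:1 in parallel, and no patient is matched to a patient in the other arm. A paired t-test can therefore only compare month 6 (or month 3) with baseline inside one arm. The same holds for Wilcoxon's test if the signed-rank version is meant. That is the likelier reading, because the section names the Mann-Whitney test separately, but the text does not settle it. The paired t-test carries the point on its own.

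A within-arm test answers whether the arm changed, not whether vitamin D changed it. The plan offers it as a test of the secondary outcomes at the 0.05 threshold, and does not say that an efficacy statement must rest on the between-arm comparison. A report that follows the text could thus present a significant change on vitamin D, with a non-significant one on placebo, as an effect on insulin resistance, SF-36, lipids or blood pressure. Such a pattern does not show a treatment effect, because the difference between the arms has not been tested.

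Changes common to both arms are plausible here. For example, participants are told their blood pressure and anthropometry during the trial, and blood pressure is a secondary outcome.

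**Working it through.** **The plan's own figure.** This point rests on no stated number, but the sample size shows the conventions in use. It is set "to demonstrate a significant difference at 80% power and 5% significance" and "aimed at a difference of 0.5% in HbA_1c_ value in the treated group as compared to the placebo group". The SD that it assumes is 1.0%. With a two-sided 5% level, n per arm = 2 × (1.960 + 0.842)² × 1.0² / 0.5² = 62.8, rounded up to 63, or 126 in total. The stated 126 is reproduced, with power 80.1%. I use the two-sided 5% level below as well; sidedness is not stated for the tests.

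**Inputs.**
- Evaluable patients per arm: 300 × (1 − 0.20) / 2 = 120, from the recruited number, expected dropout and 1:1 allocation. With no dropout it is 150.
- True vitamin D effect: none.
- Change common to both arms, s, in SDs of the within-patient change: **assumed** at 0 to 0.3, because the documents give no value.

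**Paired test in the vitamin D arm.** Under a shared change s, the paired t statistic follows a noncentral t distribution with n − 1 degrees of freedom and noncentrality s√n. For s = 0.2 and n = 120 the noncentrality is 0.2 × 10.95 = 2.19, against a critical value of 1.98. The rejection probability is p = 0.584.

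**Significant on vitamin D, not on placebo.** The arms are independent and have the same p, so the probability is p(1 − p). At s = 0.2 this is 0.584 × 0.416 = 0.243.

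| Shared change s | n per arm | Paired test significant on vitamin D | Significant on vitamin D, not on placebo |
|---|---|---|---|
| 0 | 120 | 0.050 | 0.048 |
| 0.1 | 120 | 0.192 | 0.155 |
| 0.2 | 120 | 0.584 | 0.243 |
| 0.3 | 120 | 0.903 | 0.087 |
| 0.1 | 150 | 0.229 | 0.177 |
| 0.2 | 150 | 0.682 | 0.217 |
| 0.3 | 150 | 0.955 | 0.043 |

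The last column cannot exceed 0.25, its value at p = 0.5. It falls again for larger shifts because placebo then also becomes significant.

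**Between-arm test of the changes.** A shared change cancels in the difference between arms. In 20,000 simulated trials with 120 per arm, a two-sample t-test on the changes rejected in 5.2%, 4.9% and 4.7% at s = 0, 0.2 and 0.3, which is the nominal 5% within simulation error.

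**Raw changes against baseline adjustment.** Let σ be the SD at each visit, assumed equal, and r the correlation between baseline and follow-up. The variance of a raw change is 2σ²(1 − r). The residual variance after adjustment for baseline is σ²(1 − r²). The ratio is (1 − r²) / [2(1 − r)] = (1 + r)/2, which is 0.75 at r = 0.5 and 0.85 at r = 0.7. Both values of r are assumptions.

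**The case against.** The strongest reply is that the plan does contain a valid comparison. Repeated measures analysis of variance is one of the three listed methods, and it is the method used between arms for HbA1c. The next sentence compares changes between treatment and placebo. That stands. A reader might infer that the secondary outcomes are to be judged by within-arm tests alone, or that 58% or 24% is the plan's false-positive rate. The documents support neither. No sentence says that significance in one arm only will be read as an effect. The percentages apply only if the within-arm result is used for the conclusion, and only at the assumed shift.

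Two mechanisms that a reader might cite for a shared change are weak here. *Season*: inclusion is spread over one year and the results are to be adjusted for season (Phase II of the study procedure). With even enrolment a yearly cycle would largely average out of the mean change. *Regression to the mean*: eligibility selects on HbA1c and on limits for 25(OH)D, calcium, phosphate and renal function. It does not select on SF-36, HOMA, lipids, blood pressure or skin AGEs, so the effect is not shown for those outcomes.

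The choice between raw change and baseline adjustment is one of efficiency. Both are unbiased in a randomised trial, and the text does not actually call the delta comparison unadjusted.

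Finally, a condensed article may leave model details to an analysis plan that is not shown. That covers the exact model, but not the paired t-test, which this document itself names as a test for the secondary outcomes.

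**Conclusion.** The point holds in a limited form. The plan lists a paired t-test, and probably a signed-rank test, as inferential tests for the secondary outcomes in a parallel-arm trial. Beside them it places a between-arm comparison without a named test, and it does not say which result decides. The within-arm tests cannot attribute a change to vitamin D.

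With no true effect, 120 per arm and an assumed shared change of 0.1, 0.2 or 0.3 SD of the change, the vitamin D arm alone would test significant in about 19%, 58% or 90% of trials. The pattern of significance on vitamin D only would occur in about 16%, 24% or 9%. The between-arm comparison stays at 5% throughout. These figures show what depends on the choice of test; they do not predict this trial's results.

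The HbA1c analysis is explicitly between arms and is not affected, and no sample size changes. The matter is worth correcting because insulin resistance and quality of life are both stated objectives.

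**What to change.** Remove the paired t-test and Wilcoxon's test as inferential tests for the secondary outcomes, and replace the two sentences with wording such as:

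> Each continuous secondary outcome is compared between the randomised arms with adjustment for the baseline value of that outcome. Outcomes measured at 0 and 6 months are analysed by analysis of covariance at month 6. Outcomes also measured at month 3 are analysed by a repeated measures model for months 3 and 6 with arm, visit, arm-by-visit interaction and the baseline value. The result is the adjusted between-arm difference with its 95% confidence interval. Within-arm changes are descriptive and are reported without p-values.

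Keeping month 3 matters for blood pressure, fasting glucose, insulin, C-peptide and 25(OH)D, which Table 1 schedules at all three visits. A month-6-only analysis would discard those data. For clearly skewed outcomes the same model can be fitted on the log scale, with the result given as a ratio.

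The cost is wording only: no new data, visits or patients, since the baseline values are already collected. Within-arm p-values disappear from the report. In return, the variance falls to (1 + r)/2 of that of raw changes, for example 0.75 at an assumed r of 0.5.

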Vitamin D is a secosteroid that is obtained from dietary sources, either food or supplements, and exposure to sunlight. It needs to be hydroxylated twice to become biologically active. Vitamin D is transported to the liver where it is first hydroxylated by 25-hydroxylase into 25-hydroxyvitamin D (25 (OH) D). This is the major circulating form used as an indicator of vitamin D status. The second hydroxylation occurs in the kidney by 1α-hydroxylase (1α-OHase), a product of the CYP27B1. Here the largest amount of the biologically active form of vitamin D: 1,25 dihydroxyvitamin D (1,25 (OH) 2D) is formed. Besides its classical role in calcium and bone homeostasis, vitamin D deficiency has recently been identified as contributing factor in the onset of insulin resistance in T2DM [5,6]. In a meta-analysis of observational studies a relatively consistent association between low vitamin D status and the prevalence of T2DM or metabolic syndrome was reported [6]. However, due to confounding and selection bias in epidemiological studies, a causal link cannot be established. To determine whether the relation between vitamin D deficiency and glycaemic control is causal in nature, randomised controlled trials with vitamin D supplementation are needed. To date, only few clinical trials examining this relation, with glycaemic control as primary outcome in T2DM, have been performed [7-13]. The results of these clinical trials are inconsistent mostly due to the small sample size, low dose of vitamin D supplementation and short duration of the trials. Recently, a meta-analysis done by George et al. [14] demonstrated a small effect of vitamin D supplementation on fasting glucose and insulin resistance, with no effect on HbA_1c_. However most of these reviewed studies did not include diabetic patients nor had insulin resistance as primary outcome [15-22]. Therefore, adequately powered, randomised placebo-controlled clinical trials with vitamin D supplementation are needed.

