#### Phase II

The trial has a total of three visits at the patient’s own general practice (Figure 1). The initial visit includes informed consent, assessment of eligibility, questionnaires regarding demographics, sunlight exposure, physical activity, dietary intake (fish and dairy products), diabetes history and medication, co-morbidity and health related quality of life (SF-36). Anthropometric parameters and skin AGE accumulation will be measured. Blood collection will be collect at this stage. The study medication will be given for six months with a prior instruction. The second visit at three months is for safety assessment and observation of consumption. This includes: discussion of any adverse events, any change in medication, control of the ingestion of the study medication, blood collection (including serum calcium, renal function, serum 25 (OH) D and HbA_1c_). The final visit is at the end of six months, when questionnaires and anthropometric measurements are repeated and the last set of blood samples are collected (Table 1). The inclusion of all patients will be spread over one year to prevent large seasonal influences, as well as the results will be adjusted for seasonal influences.

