**Figure 1 F1:**
[figure not shown]
Recruitment flow chart.

**Table 1 T1:** Outcome variables and time of measurement (n = 300)

**Variables**	**Months**		
	0	3	6
Informed Consent	x		
Sociodemographics	x		
Medical and family history	x		
Diet, sun exposure, physical activity	x		x
Advanced Glycation End products (AGEs)	x		x
Questionnaire SF-36	x		x
Medication alterations		x	x
Adverse events		x	x

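### The covariate list meant to remove confounding of vitamin D status omits sun exposure, which the trial measures; the non-randomised analyses are open to residual confounding that is possible but not shown

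*Protocol article*

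**What the plan says.** In the protocol article, the Statistical analysis section plans a logistic or linear regression as a "multivariate analysis to relate an outcome variable to causal variables". It gives the purpose of this analysis as being to "rule out the possible role of confounders for vitamin D deficiency". The items named are "season of measurement, maternal age, ethnicity, diet, physical activity and BMI".

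Three other places bear on that list:

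- The Background says vitamin D comes from dietary sources, "either food or supplements, and exposure to sunlight".
- Phase II describes first-visit "questionnaires regarding demographics, sunlight exposure, physical activity, dietary intake", with questionnaires repeated at the final visit. Table 1 carries the row "Diet, sun exposure, physical activity", marked at months 0 and 6.
- Phase II also says inclusion is spread over a year and that results will be adjusted for season.

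No sentence on analysis names sun exposure.

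**The concern.** The list takes two of the three items in one Table 1 row and leaves out the third without giving a reason. The omitted item is the one that the Background names beside diet as a source of vitamin D. Season is only a partial stand-in: it is the same for everyone measured in a given month, while personal exposure differs between them.

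What is at stake is the set of analyses that randomisation does not protect. Objective iii, the association of skin autofluorescence with serum vitamin D, is one of them. If such an association is adjusted by regression, its credibility depends on the covariates chosen.

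The wording adds to the difficulty. No covariate list can exclude confounding, and the article itself says of earlier observational work that "due to confounding and selection bias in epidemiological studies, a causal link cannot be established". Calling the regressors causal and promising to exclude confounders sits badly with that sentence.

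**Working it through.** No figure in the article states or implies the size of this effect, so there is no plan figure to reproduce. The check has three parts.

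**1. The text side by side**

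| Item | Named as a vitamin D source (Background) | Measured (Table 1) | In the covariate list |
|---|---|---|---|
| Diet | yes | months 0 and 6 | yes |
| Sun exposure | yes | months 0 and 6 | no |
| Physical activity | no | months 0 and 6 | yes |

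The omission is confirmed.

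**2. What the omission could do**

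Let *a* be the correlation of sun exposure with 25(OH)D, and *b* its correlation with the outcome by routes other than vitamin D. Both are taken after adjustment for the listed covariates. Suppose vitamin D has no true association with the outcome. The spurious partial correlation is then

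r = a × b.

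With six covariates (one term each) and a two-sided 5% test, the Fisher z approximation gives

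m = atanh(r) × √(n − 3 − 6), and P(p < 0.05) = 1 − Φ(1.96 − m) + Φ(−1.96 − m).

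Inputs: n = 300 from the sample size section, and n = 300 × 0.8 = 240 after the expected 20% dropout. The documents give neither *a* nor *b*; all values below are assumptions.

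Worked case, a = 0.3, b = 0.2, n = 300: r = 0.06 and m = 0.0601 × √291 = 1.025. So P = 1 − Φ(0.935) + Φ(−2.985) = 0.176.

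| a | b | r | n = 300 | n = 240 |
|---|---|---|---|---|
| any | 0 | 0 | 5.0% | 5.0% |
| 0.2 | 0.1 | 0.02 | 6.3% | 6.1% |
| 0.3 | 0.1 | 0.03 | 8.1% | 7.4% |
| 0.3 | 0.2 | 0.06 | 17.6% | 15.0% |
| 0.4 | 0.2 | 0.08 | 27.7% | 23.0% |
| 0.4 | 0.3 | 0.12 | 53.9% | 44.9% |

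The first row is the important one. However strongly sun exposure predicts 25(OH)D, leaving it out creates no spurious association unless *b* differs from zero. If it is added and measured without error, the rate returns to 5%.

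**3. What adding it could cost**

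If sun exposure predicts 25(OH)D but has no other link to the outcome, adjusting for it multiplies the variance of the vitamin D coefficient by about 1/(1 − a²):

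- a = 0.2: 1/0.96 = 1.04, or 4% more variance
- a = 0.3: 1/0.91 = 1.10, or 10% more
- a = 0.4: 1/0.84 = 1.19, or 19% more

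Interval width grows by the square root, so by about 2% to 9% over this range.

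**The case against.** The strongest reply is that a source of vitamin D is not thereby a confounder. Confounding also needs a route from sun exposure to the outcome that bypasses vitamin D and the listed covariates, and the article states none. Outdoor activity is at least partly covered by physical activity. The AGE reading is taken on the forearm, but nothing in the article says that sunlight alters it. This objection stands, and it is why bias can be called possible but not shown.

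Season and physical activity are already listed, so only what remains of sun exposure after them matters. That also stands, though it reduces the problem without removing it.

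The word introducing the list may mean *such as*, and a condensed article need not give every covariate. This is fair, and it weakens any claim that sun exposure will certainly be left out. It does not explain why two items of a three-item row were chosen. If the list is open, naming the variable settles the matter.

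A reader might infer that a false association will appear and be reported as causal. The documents do not support that. Objective iii speaks of an association, the Discussion only of a potential causal association, and the Background warns against causal reading of confounded data. The regression is not expressly tied to objective iii either; the correlation coefficients planned in the same section may serve it. What remains is loose wording.

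Finally, adjustment is not free, as the variance calculation shows. The cost is modest, and the plan already accepts the same kind of cost for season and diet.

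**Conclusion.** The point holds as a minor one. Sun exposure is measured at months 0 and 6 and named as a source of vitamin D, but it is missing from a list whose declared purpose is to deal with confounders of vitamin D deficiency. The consequence is confined to non-randomised analyses of 25(OH)D status. The primary HbA1c analysis compares randomised arms by intention to treat and is untouched, as is the sample size.

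The size cannot be fixed from the documents. The false-positive rate is 5% if sun exposure has no separate route to the outcome. Over the assumed non-zero correlations tabulated, it runs from about 6% to 54% at n = 300. The upper end should not be read as an estimate: it needs partial correlations of 0.4 and 0.3 to survive adjustment for every listed covariate, and nothing in the article supports either value.

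Separately from any figure, the promise to exclude confounding is too strong for any covariate list, and more so for one that relies on questionnaire measures.

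**What to change.** In the Statistical analysis section:

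- Add baseline sun exposure to the covariates for regressions on vitamin D status, including any regression of skin autofluorescence on 25(OH)D. Report the vitamin D estimate with and without it, so that a change in the estimate can be told apart from a loss of precision.
- Replace *rule out* with *adjust for*, and *causal variables* with *explanatory variables*. State that causal conclusions rest on the randomised comparison.
- In the same edit, check *maternal age*, which does not fit a population of adults with type 2 diabetes.

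The variable is already collected, so there is no new data burden. The analysis cost is one or two degrees of freedom out of 300, plus the possible modest widening of intervals shown above. The two sets of estimates would make that widening visible.

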### Inclusion/exclusion criteria

Adults (≥18 years) with T2DM, diagnosed according to the World Health Organisation, who are treated with lifestyle advises, metformin, or sulfonylurea-derivatives (SU-derivatives), whether or not in combination, were invited for participation. Serum glycated hemoglobin (HbA_1c_) had to be stable and below or equal to 64 mmol/mol (8.0%) for the last three months without recent changes in hypoglycaemic agents.

The exclusion criteria are: an impaired renal function (estimated creatinine clearance < 30 ml/min measured by the MDRD formula: 186 × (serum creatinine)^ -1.154 × (age)^ -0.203 × 0.742 (if the subject is female) or × 1.212 (if the subject is black)), any granuloma forming disorder, known history of renal stones or hypercalcaemia (serum calcium > 2.65 mmol/l), hypo- or hyperphosphatemia, serum 25 (OH) D < 15 nmol/l or > 150 nmol/l, known intolerance for cholecalciferol, using other antidiabetic treatment as mentioned above, insufficient knowledge of the Dutch language, mental retardation or psychiatric treatment for schizophrenia or bipolar disorder, participation in any other trial, being pregnant or lactating, or no signed informed consent.

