This trial has several strengths: the study sample size allows us to perform a subgroup analysis of vitamin D deficient patients. Taken into account that only in vitamin D deficient patients an effect of vitamin D supplementation on glycaemic control will be found, we chose to recruit double the number of participants as calculated with the power estimation, hypothesizing that 50% of the included patients will be vitamin D deficient (serum 25 (OH) D < 50 nmol/l). Secondary, the relatively high dose chosen for intervention and the duration of the trial are strengths of our study. The dose of vitamin D supplementation of 50,000 IU of vitamin D per month (daily equivalent ~1667 IU) is based on the recommendations of the Institute of Medicine and on the study done by van Groningen et al. [31,34]. In this latter study, performed in the Netherlands, it was demonstrated that a cumulative dose of 100,000 IU given in 2 months increases the serum 25 (OH) D meanly with 29 nmol/l. Assuming that the mean serum 25 (OH) D in our study population will be around 50 nmol/l at baseline, the serum 25 (OH) D should be raising to a sufficient status (≥75 nmol/l) in two months. To measure a difference in HbA_1c_ level we hypothesize that the maximal effect will be seen at least at six months, regarding the fact that the red blood cells circulate about 100 days in the blood and HbA_1c_ levels takes around six weeks to change. Furthermore, this is the first study examining the association between vitamin D status and skin autofluorescence value as well as the effect on skin AGEs after vitamin D supplementation. For this secondary outcome the duration of our trial will be a limitation, regarding the stability and long half-life of skin AGEs with could be the cause to find no effect of vitamin D supplementation on skin AGEs.

The results of this trial should provide more insight into the potential causal association between vitamin D status and glycaemic control in patients with T2DM.

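### The confounder list names maternal age, which has no role in this trial, and does not name the participant's own age, so non-randomised associations such as objective iii are open to confounding by age

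*Protocol article*

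**What the plan says.** The Statistical analysis section of the protocol article describes correlation coefficients and then a regression step: "A logistic and/or linear regression model will be used for multivariate analysis to relate an outcome variable to causal variables". It gives the purpose as ruling out the role of "confounders for vitamin D deficiency as season of measurement, maternal age, ethnicity, diet, physical activity and BMI". This is the only place in the article that names covariates for a multivariable model. The primary HbA1c analysis has its own sentence earlier in the section, which adjusts for baseline characteristics without naming them.

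The third objective, at the end of the Background, is "To investigate the association between skin autofluorescence and serum vitamin D". The Discussion presents this as the first study of that association.

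The Inclusion/exclusion criteria define the population as "Adults (≥18 years) with T2DM, diagnosed according to the World Health Organisation", and the exclusions end with "being pregnant or lactating, or no signed informed consent".

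**The concern.** A confounder list is operative text: whoever fits the model will take the covariates from it. One entry here belongs to another kind of study, such as one of mothers and children. The covariate one would expect in its place, the age of the person measured, is not named.

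Randomisation protects the comparison of vitamin D with placebo. It does not protect objective iii, which relates two measured quantities, skin autofluorescence and serum 25(OH)D, across participants. If age goes with both, an unadjusted analysis, or one adjusted for the listed covariates only, can show an association that reflects ageing and not vitamin D. At stake is the interpretation of a stated objective that the article counts among the study's novelties.

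**Working it through.** The article gives no figure on this point to reproduce. The check is first a comparison of sections and then an illustration of size under assumed values.

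**1. Does maternal age belong to this design?**
- The participants are adults with type 2 diabetes, and pregnant or lactating women are excluded (Inclusion/exclusion criteria).
- The initial visit covers "questionnaires regarding demographics, sunlight exposure, physical activity, dietary intake (fish and dairy products), diabetes history and medication, co-morbidity" and quality of life (Phase II). Maternal age is not mentioned.
- Table 1 has no such row. Its rows for sociodemographics and for medical and family history are not itemised.

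Maternal age therefore appears once in the article, in the confounder list, with no role in the design and no described source.

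**2. Is the participant's own age available?**
Yes. It is needed for the lower age limit and for the renal criterion, "estimated creatinine clearance < 30 ml/min measured by the MDRD formula: 186 × (serum creatinine)^ -1.154 × (age)^ -0.203". It also falls under the demographics taken at the initial visit. It is not named in the confounder list.

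**3. Which analyses depend on the list?**
- HbA1c by randomised arm: allocation balances age in expectation, and baseline adjustment is stated separately. The list does not bias this comparison.
- Objective iii: not randomised. The correlation and regression methods in the same part of the section are the only ones described that fit it.

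**4. Does the article give reason to think of age?**
Only indirectly. The Background cites a 47.8% prevalence of deficiency among older people, with no younger group for comparison. The Discussion refers to a trial-duration limit "regarding the stability and long half-life of skin AGEs", which is consistent with build-up over time but does not mention age.

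**5. How large could the effect be? (illustration, assumed inputs)**
Let *a* be the correlation of age with skin AGEs and *b* that of age with 25(OH)D. If there is no association given age, the partial correlation is zero, so the unadjusted correlation is

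r = a × b.

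The article gives neither *a* nor *b*. I assumed *a* from 0.1 to 0.4 and *b* from -0.05 to -0.3. The chance that a two-sided 5% test rejects at n = 300 follows from Fisher's z: with m = atanh(r) × √(300 − 3) = atanh(r) × 17.23, it is Φ(−1.96 − m) + 1 − Φ(1.96 − m).

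| a | b | r = a × b | chance of p < 0.05 |
|---|---|---|---|
| 0.1 | -0.05 | -0.005 | 5.1% |
| 0.2 | -0.1 | -0.02 | 6.4% |
| 0.3 | -0.2 | -0.06 | 17.9% |
| 0.4 | -0.2 | -0.08 | 28.2% |
| 0.4 | -0.3 | -0.12 | 54.7% |

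At the low end the test keeps essentially its nominal 5%. At the high end it would declare a non-existent association about as often as not. These figures ignore any part of the age effect that the other listed covariates would absorb.

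**The case against.** The strongest defence is that this is a one-word slip for age. The population is adult and age must be known for eligibility, so a sensible analyst would read the entry that way. On that reading age is in the set and the gap closes. In addition, the word before the list may mean 'such as', so the list need not be complete. Both points are plausible. They make the remedy easy, but they do not make the printed entry right: a named covariate is wrong, and the reader has to guess what was meant. Nor is this a detail left to an analysis plan, because the article chose to name the confounders.

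Three further inferences are tempting, and the article does not support them:
- **That the model could not be fitted.** Two rows of Table 1 are not itemised and the case record form is not shown. One can say only that the article lists no such item. An open list could also be fitted without it.
- **That objective iii is confounded.** The regression text is not tied to objective iii by name, and the article's support for a link of age with either variable is indirect. Open to confounding by age is as far as the text goes.
- **That treatment effects will be adjusted for covariates measured after randomisation.** Table 1 repeats diet, physical activity and BMI after month 0, but measuring something again is not a plan to adjust for it. For the primary analysis the article specifies baseline characteristics. Season of measurement is a calendar fact that treatment cannot change, so its place in the list needs no restriction.

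**Conclusion.** The point holds as an error in the analysis text. Maternal age has no place in the covariate set, and the participant's own age, which the trial holds, is not named. Followed literally, the model would leave non-randomised associations, objective iii above all, open to confounding by age.

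The direction and size of any bias cannot be derived from the article. The range of -0.005 to -0.12 for a spurious correlation rests on the assumed age correlations, on no true association given age, and, for the rejection rates, on all 300 participants contributing data. It shows that the bias could be trivial or material, and no single value in it should be read as an estimate.

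A reader might infer that the main result is compromised. It is not: the HbA1c comparison is between randomised arms and does not depend on this list. The point is minor in consequence, certain as to the wording, and cheap to settle.

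**What to change.** In the Statistical analysis section, replace maternal age with participant age at baseline in the list of confounders. Add one sentence saying that this covariate set applies to the regression relating skin autofluorescence to serum 25(OH)D.

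The cost is one line of text. Age is already known for every participant through the eligibility check, so no data collection, visit or sample size changes. The correction is best made before the objective iii analysis is run, so that including age is seen to be planned and not chosen after looking at the result.
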